Regarding PP2, based on clinical experience and questionnaire information from the recruitment centers as part of the design preparations, an estimated 33% of 3331 patients (*n* = 1,099) with a clinical diagnosis of at least moderately severe MDD are assumed to be still suicidal ≥ 48 h after admission. Approximately 60% of this group are expected to consent to participate in the interview-based study (and the naturalistic, 6-month follow-up study, should they also fulfill criteria for PP3, determined during participation in PP2). The following analyses of congruence between clinical diagnosis and research diagnosis (gold standard) of at least moderately severe MDD will take place:(a) two groups will be formed (primary analysis), i.e., positive vs. negative validation of the clinical diagnosis with the research-based interview M.I.N.I.,(b) use of descriptive statistics to estimate proportions of patients meeting the gold standard of research diagnosis and their confidence intervals (see a, hypothesis 2A), as defined by diagnostic concordance with the clinical diagnosis at the time of hospitalization; and.(c) to perform multiple mixed logistic regression analysis with backward elimination to compare patients with positively validated and non-validated at least moderately severe MDD (see a, hypothesis 2B), with random factors to account for clustering of patients in centers.

Regarding PP3, the OASIS-D study was initiated with the assumption that approximately 50% of the 520 patients surveyed in PP2 would not meet ICD-10 criteria for the inclusion criteria of at least moderately severe MDD, so that260 patients would be enrolled in PP3. Assuming a 20% drop out rate, this would yield n = 208 with data at 6 months. During the interim analysis 2, in September 2022, we noted a higher drop-out rate of 34% in PP3 than the 20% expected attrition rate at the time of the study design. Due to this finding, the number of patients in PP3 was increased to n = 315, so that with an attrition rate of 34%, the number of patients with data at month 6 would remain at n = 208. Since there was a higher than initially projected transition rate from PP2 to PP3, so that the n of patients entering PP2 did not need to be increased.

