Hypotheses 3A and 3C will be analyzed by means of methods for count data, such as Poisson or Negative Binomial models, depending on whether overdispersion is present in the data or not. The dependent variable will be overall duration of PASI during the 6-month observation period and the independent variable of main interest will be time to remission of suicidal symptoms after baseline.

Hypotheses 3B and 3D will be analyzed by using Cox proportional hazard models, where the dependent variable will be time-to-first-recurrence of PASI and the independent variable of main interest will be time to remission of suicidal symptoms after baseline.

Further independent variables for regression analysis will include patient, illness, and treatment variables, including severity of depressive symptoms (MADRS, Quality of Life in Depression Scale (QIDS-S) [79]), manic symptoms (YMRS), anxiety (BAI), anger/hostility (STAXI, AF-BP), global illness symptoms (CGI-S), quality of life (EQ-5-DL), and suicidality (S-STS); presence of psychiatric emergencies; number of lifetime depressive episodes; duration of current depressive episode; nonadherence to pharmacological and nonpharmacological treatments; and comorbid borderline personality and substance abuse. Additionally, a random factor accounting for clustering of patients in centers will be added to the models.

Assuming a minimum requirement of 10 patients per predictor variable in regression analyses [91–93] and approximately 20 independent patient, illness, and treatment variables that would be tested as potential correlates of time to remission of suicidality, we estimated that a sample size of at least 200 would be required.

Additionally, as a secondary analysis, we will divide patients into two groups using the median time up to the first S-STS value of zero, which are either below or above the median time to first complete remission of suicidality.

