Furthermore, comparisons between the slower and faster remitting group of continuous variables will be performed using multiple comparison procedures (MCPs) with 3 measurement time points (T1, T2, and T4). Because only the primary outcome and very limited other parameters are collected by telephone at T3, data at T3 are not included in these analyses. Because the timing at T2 (hospital discharge) is variable, and this timing is not independent of the outcome measured, the duration between T1 and T2 is included as a covariate in the analyses. Cross-group comparisons of dichotomized or categorical variables are performed using chi-square statistics. For ease of comparison, continuous outcomes, such as depressive symptoms and medication use are calculated. All analyses are two-sided, with alpha = 0.05. Due to the exploratory nature of the study, no adjustment for multiplicity between different endpoints is conducted. Hence, p-values and confidence intervals need to be interpreted in a hypothesis-generating manner. In addition, multivariable regression analysis with backward selection will be performed to identify independent moderators or mediators of continuous and categorical outcomes, respectively. Moreover, missing continuous data will be treated using multiple imputation using chained equations and random effects for the clustering of patients in different centers.

Among the exploratory objectives, the patient, illness, and treatment factors that influence the risk of different levels of active suicidality are identified: i) active suicidality (S-STS item 3), ii) active suicidality with preparatory action (S-STS item 12), iii) self-injurious behavior without suicidal intent (S-STS item 13), and iv) suicide attempt (S-STS item 14) during the observation period of inpatient treatment and within 6 months of study inclusion (T1). Target parameters i)-iv) are associated with slower initial resolution of suicidality (lower than median time to S-STS score = 0); and with: Depressive symptom severity (MADRS, QIDS-S), manic symptoms (YMRS), anxiety (BAI), anger/hostility (STAXI, AF-BP), and global illness symptoms (CGI-S); higher number of lifetime depressive episodes; more frequent psychiatric emergencies; longer duration of current depressive episode; non-adherence to pharmacological and non-pharmacological treatments; comorbid borderline personality; and substance abuse diagnoses.

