Several limitations of the OASIS-D study need to be considered. First, OASIS-D is an observational study, not an intervention study. Consequently, treatments are based on clinical decisions that may vary from clinician to clinician and clinic to clinic. This heterogeneity may bias the analysis of treatment outcomes and factors. On the other hand, this factor increases the generalizability of the findings. Second, six of the eight participating centers are University-based clinics, which might influence the patient population in PP1 and, possibly diagnostic accuracy in PP2. However, most of the 6-month follow-up duration in the prospective study of PP3 will be in community outpatient settings, increasing the generalizability of those findings. Third, the data in PP1 are limited to routine clinical data only, as the goal is a large sample and consecutive inclusion of inpatients, which required anonymous data acquisition as part of a chart review, not requiring informed consent. This approach may lead to gaps in the data that relied on clinical documentation, as more extensive data collection beyond routine clinical data, was not possible. Fourth, speed of offset and timing and duration of recurrence of different levels of suicidality are a key outcome. Although for example continuous ecologic momentary assessment of suicidality would have been able to ensure more fine-grained assessments of suicidality trajectories [115, 116], for feasibility purposes this study relies on intermittent interviews (baseline, discharge, 3 months and 6 months) to assess the period incidence and prevalence of suicidality. This approach could lead to recall bias that may affect the data, even though we are using the S-STS as a structured interview in order to improve the quality of the data. Finally, although treatments and service utilization are also a focus of this study, we will rely on patient report, for these outcomes too, which similarly could be subject to recall bias. Nevertheless, structured interviews are employed to mitigate this effect.

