On the other hand, strengths of the OASIS-D study lie in the characterization of a consecutive epidemiological sample of hospitalized patients with MDD from eight major psychiatric centers across Germany in analysis, the in depth assessment of the diagnostic accuracy of at least moderate MDD and passive or active suicidality, including correlates, as well as prospective observation of patients with a verified diagnosis of MDD and suicidality over a 6-month period with regards to the course of their suicidality, related treatment and outcomes.

Results of the OASIS-D study are expected to inform clinical care with regards to a more detailed understanding of risk factors for different levels of suicidality in hospitalized patients with MDD, correlates of diagnostic accuracy or imprecision, as well as the course and correlates as well naturalistic treatment effects and outcomes of suicidality in patients with moderate-to-severe MDD starting from inpatient and followed through outpatient settings.

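### For treatments started after T1, comparing slower with faster remitters (or regressing time to remission on ever/never treatment) makes them look as if they delay remission

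*Protocol article*

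**What the plan says.** All references are to the Protocol article.

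- *Sample size and statistical analyses*, PP3 sample-size rationale: the count of predictors is given as "approximately 20 independent patient, illness, and treatment variables that would be tested as potential correlates of time to remission of suicidality". Ten patients for each of these gives the stated minimum of 200.
- Same section, secondary analysis: patients are divided at the median time to the first S-STS value of zero. Continuous variables are compared between the slower and faster groups at T1, T2 and T4, and categorical ones by chi-square. The same paragraph states: "For ease of comparison, continuous outcomes, such as depressive symptoms and medication use are calculated". The T1-T2 interval is added as a covariate because discharge timing depends on the outcome. Backward selection for moderators or mediators is also planned. "All analyses are two-sided, with alpha = 0.05", with no multiplicity adjustment, so results are to be read as hypothesis-generating.
- *Table 1*: routine treatment is documented for PP3 at T1, T2, T3 and T4. This covers medication, with reasons for starting, stopping and switching, and electroconvulsive therapy.
- *Discussion*, limitations: treatment follows clinical decisions that differ between clinicians and clinics, and "This heterogeneity may bias the analysis of treatment outcomes and factors". The closing paragraph nevertheless expects information on "naturalistic treatment effects and outcomes of suicidality in patients with moderate-to-severe MDD".

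No time-dependent coding, landmark or other alignment of treatment start with remission is described.

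**The concern.** The slower and faster groups are defined by the outcome, and treatment recorded over the following months is then compared between them. Two mechanisms push the same way.

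- **Time at risk.** A patient who remits on day 10 has ten days in which a treatment can be added while suicidal. One who remits on day 100 has a hundred.
- **Indication.** Some treatments are added because suicidality persists. The *Background* itself describes one option for chronic suicidality and another as a last resort.

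A treatment that does nothing would therefore appear more often among slower remitters. The same holds for a regression of time to remission on whether the treatment was ever received. The direction is systematic, so a larger sample only makes the wrong answer look firmer. A reader could conclude that treatments reserved for persistent suicidality prolong it. The *Background* hopes that the results may help to define a standard of care for later comparator studies, so such a conclusion could carry forward.

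**Working it through.** **1. The plan's own figures.** 10 × 20 = 200. 260 × 0.80 = 208, as in "Assuming a 20% drop out rate, this would yield n = 208 with data at 6 months". After the increase to 315 with 34% attrition, 315 × 0.66 = 207.9. These reproduce and are not in dispute. A median split of 208 gives 104 per group.

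**2. Assumptions.** The article gives no remission or treatment-start rates. Assume exponential time to remission with median 30 days, so λ = ln 2 / 30 = 0.0231 per day; treatment started at a = 0.01 per day while still suicidal; no effect on remission; no starts after remission.

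**3. Share treated in each half.**

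- λ/(λ + a) = 0.0231/0.0331 = 0.698, and e^(−30a) = e^(−0.3) = 0.741.
- Faster half, untreated: 0.698 × (1 − 0.5 × 0.741)/0.5 = 0.879, so 12% treated.
- Slower half, untreated: 0.741 × 0.698 = 0.517, so 48% treated.
- Odds ratio: (0.483/0.517)/(0.121/0.879) = 6.8.
- Expected z at 104 per group: pooled share 0.302, standard error √(2 × 0.302 × 0.698/104) = 0.064, z = 0.362/0.064 = 5.7.

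With medians of 14, 30 or 60 days, start rates of 0.5%, 1% or 2% per day, and follow-up cut at 183 days, the same calculation gives odds ratios of 5.8 to 12.8. The true value is 1.

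**4. Dilution by starts after remission.** Now count starts over all 183 days, with rate b per day after remission. The chance of being untreated for a patient remitting at time T is e^(−aT − b(183 − T)). Averaging over each half (median 30 days, a = 1%):

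| b per day | Faster treated | Slower treated | Odds ratio |
|---|---|---|---|
| 0 | 12% | 48% | 6.7 |
| 0.25% | 43% | 62% | 2.2 |
| 0.5% | 62% | 72% | 1.5 |
| 1% | 84% | 84% | 1.0 |

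(6.7 rather than 6.8 because follow-up is cut at 183 days.) The bias is large for treatments started mainly because suicidality persists, and vanishes for treatments started at the same rate regardless.

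**5. Simulation of the regression version.** 208 patients, 182 days, no true effect, median remission 14, 30 or 60 days, mean wait to treatment start 30, 90 or 180 days, treatment counted only up to remission.

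- Ever/never as a fixed covariate: hazard ratio for remission 0.14 to 0.45, significant in 95% to 100% of runs. Chi-square between the halves: significant in 93% to 100%.
- Adding T1-T2 duration (median 30 days, mean wait 90 days, assumed correlation with remission time 0.3 or 0.7): hazard ratio 0.37 or 0.44, significant in every run. Without it, 0.36.
- Time-dependent coding: hazard ratio 0.96 to 1.03. The scenario with the highest rejection rate (11% of 150 runs), repeated with 1,500 runs, gave 1.00 and 4.7% rejection.
- Treatment already in place at T1 and unrelated to prognosis: hazard ratio 0.98 to 1.02, rejection 4.5% to 7%.

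**The case against.** A reader might infer that the plan codes treatments as fixed ever/never variables throughout, that most treatment begins after T1, and that the main PP3 results are therefore compromised. The article does not support that.

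- It never states how treatments are coded in the regressions; an analysis plan not shown may settle this.
- Time to remission is named as an outcome for treatment variables only in the sample-size sentence. In the models specified for Hypotheses 3A to 3D it is the independent variable of main interest.
- The moderators in 3C and 3D are factors at T0, and nonadherence is the only treatment-related item among the named covariates.
- Current treatment is already recorded at T1, at least 48 hours after admission. No figure shows how much starts later.
- The slower/faster split is secondary, and the results are declared hypothesis-generating. Medication use is called an outcome and compared at visits, which is not identical to cumulative ever-treated status up to remission. Its T1 comparison is free of the timing bias.

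All of this stands, and it limits the point. It does not remove it. In the slower/faster comparison the grouping comes from the outcome, so treatment begun between T1 and the later visits is compared across outcome-defined groups whatever the coding. The hypothesis-generating label is attached to multiplicity, which is random error. The stated limitation concerns variation between clinicians and clinics, not persistence driving treatment. The authors recognised that discharge timing depends on the outcome but did not extend that reasoning to treatment starts.

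**Conclusion.** The point holds for treatments started after T1, in the secondary slower/faster comparison and in any regression on time to remission that codes treatment as ever/never. There the bias is towards apparent delay of remission, and the T1-T2 covariate does not correct it. Treatments in place at T1 escape the timing artefact, although confounding by indication is still possible for them.

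The size is illustrative. For a treatment without effect, 12% versus 48% treated (odds ratio 6.8) rests on a 30-day median, starts at 1% per day while suicidal and none afterwards. Starts after remission reduce it, to nothing if they occur at the same rate. Hypotheses 3A to 3D as specified, and the sample size, are unaffected. The correction is worthwhile but not a must-fix.

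**What to change.** 1. Restrict tested treatment comparisons between remission groups, and tested treatment correlates of time to remission, to treatments in place at T1.
2. Where start dates are available, analyse later starts as time-dependent exposures (exposed from the start date) or by landmark. State that this removes the timing artefact only: confounding by changing severity remains, adjustment for T1 severity does not deal with it, and severity is re-measured only at the scheduled visits.
3. Report treatments begun after T1 by remission group as description, without tests. In the closing paragraph of the *Discussion*, speak of treatments received instead of treatment effects, and add this mechanism to the limitations.

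The cost is analysis-plan wording and a check of the treatment records. *Table 1* lists reasons for starting and switching medication but does not explicitly list start dates, so their availability must be confirmed before step 2 is promised. The downside is fewer tested treatment comparisons.

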**Methods/Results:**

OASIS-D is an eight-site, six-month, cohort study of patients aged 18-75 hospitalized with MDD. Divided into three sub-studies and patient populations (PPs), OASIS-D will (i) systematically characterize approximately 4500 consecutively hospitalized patients with any form of unipolar depressive episode (PP1), (ii) evaluate the validity of the clinical diagnosis of moderate or severe unipolar depressive episode with the Mini-International Neuropsychiatric Interview (M.I.N.I.) and present suicidality (at least passive suicidal thoughts) present ≥ 48 h after admission with the Sheehan-Suicide Tracking Scale (S-STS), assessing also predictors of the diagnostic concordance/discordance of MDD in around 500 inpatients (PP2), and (iii) characterize and prospectively follow for 6 months 315 inpatients with a research-verified moderate or severe unipolar depressive episode and at least passive suicidal thoughts ≥ 48 h after admission, evaluating treatment and illness/response patterns at baseline, hospital discharge, 3 and 6 months. Exploratory objectives will describe the association between the number of days with suicidality and utilization of outpatient and inpatient care services, and structured assessments of factors influencing the risk of self-injurious behavior without suicidal intent, and of continuous, intermittent or remitted suicidality during the 6-month observation period.

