Hypothesis 3A: We hypothesize that the time to remission of suicidal symptoms after the baseline is a major determinant of shorter overall duration of passive or active suicidal ideation (PASI) during the entire 6-month observation period.

Hypothesis 3B: We hypothesize that the rate of remission of suicidal symptoms after baseline is a major determinant of lower recurrence of PASI during the 6-month observation period.

Hypothesis 3C and 3D: We hypothesize that a longer total duration of PASI (Hypothesis 3C) and a greater risk of recurrence of PASI after complete remission (Hypothesis 3D) during the 6-month observational phase is associated with the following factors at time T0 (i.e., “moderators”): greater severity of (i) depressive symptoms [28, 36, 42, 43], (ii) manic symptoms (below the threshold of (hypo)mania as part of MDD), (iii) anxiety symptoms [28, 36, 45], (iv) anger and hostility [43], (v) quality of life impairment [48, 49], (vi) global symptoms of illness and (vii) suicidality [28, 36, 42, 47], (viii) higher number of lifetime depressive episodes, (viii) index admission as part of a psychiatric emergency, (ix) longer duration of current depressive episode [44], (x) higher non-adherence to pharmacological and non-pharmacological treatments, (xi) comorbid borderline personality disorder [35, 46], and (xii) comorbid substance use diagnosis [28].

Exploratory study aim 1 of PP3 is to describe the association between PASI and suicide attempts (S-STS item 14) as well as with the utilization of outpatient and inpatient care services during the 6-month observation period.

Exploratory hypothesis 1A, 1B and 1C: We hypothesize that a higher number of days with PASI (exploratory hypothesis 1A), a higher number of days with active suicidal ideation (exploratory hypothesis 1B) and a higher number of suicide attempts (exploratory hypothesis 1C) during the 6-month observation period are significantly associated with a higher number of (i) outpatient appointments, (ii) emergency department visits, (iii) inpatient hospitalizations, (iv) hospitalizations as part of psychiatric emergencies, (v) psychiatric hospital bed days, and (vi) suicide-related hospital bed days.

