All analyses will be performed as intent-to-treat analyses, independent of non-adherence with clinically prescribed treatments or drop out from clinical care.

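### The 3A/3C count models use time to remission as if fully observed, but patients suicidal throughout follow-up have no such time, and the faster/slower split has no stated rule for them

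*Protocol article*

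**What the plan says.** All places are in the protocol article, under Sample size and statistical analyses unless stated.

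- **3A/3C (Poisson or negative binomial):** the regressor is how long suicidality takes to remit, counted from baseline: "The dependent variable will be overall duration of PASI during the 6-month observation period and the independent variable of main interest will be time to" (the sentence ends by naming that event).
- **3B/3D (Cox):** "the dependent variable will be time-to-first-recurrence of PASI and the independent variable of main interest will be time to remission of suicidal symptoms after baseline".
- **Secondary analysis:** "we will divide patients into two groups using the median time up to the first S-STS value of zero". Patients count as faster or slower according to the side of that median on which they fall.
- **Missing data:** "missing continuous data will be treated using multiple imputation using chained equations", with random effects for centre.
- **Analysis set:** "All analyses will be performed as intent-to-treat analyses, independent of non-adherence with clinically prescribed treatments or drop out from clinical care".
- **Expected courses (abstract, Methods/Results):** "continuous, intermittent or remitted suicidality during the 6-month observation period".
- **Numbers:** 315 patients in PP3, 34% attrition, 208 with month-6 data, and a requirement of at least 200 (10 patients for each of about 20 predictors).

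The article does not mention censoring of time to remission or say where a patient without an S-STS zero belongs. The paragraph on exploratory objectives describes slower resolution as a time under the median, whereas a slow remitter has a time over it.

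**The concern.** Time to remission is right-censored. For a patient who is suicidal at every visit, all that is known is that it exceeds the follow-up time. The 3A/3C models place it on the right-hand side as an ordinary continuous covariate, which needs a number for every patient.

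The outcome of the same model is fully defined for that patient, since PASI was present for nearly the whole period. The patients with the longest outcome are therefore the ones with no regressor value, and these are the chronic courses the study sets out to describe. Deleting them cuts off the upper end of both variables. Imputing the time treats a known fact (no remission during follow-up) as an unknown number and ignores its lower bound. In both cases the estimated link between time to remission and PASI duration no longer describes the whole cohort.

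The split has a milder form of the problem. It can be applied sensibly, but its wording also permits a median taken among remitters only, with non-remitters left out of both groups.

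**Working it through.** **1. The plan's own figures.** Initial plan: 260 × 0.80 = 208. Revised plan: 208 / 0.66 = 315.2, and 315 × 0.66 = 207.9, so the stated 315 and 208 agree to rounding. Minimum: 10 × 20 = 200. The slack is 208 − 200 = 8 patients.

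**2. 3A/3C if undated completers are dropped.** Let q be the share of completers not remitted by month 6. The article does not give q; 5% to 40% is assumed. Completers with a regressor value = 208 × (1 − q). This falls below 200 once q > 1 − 200/208 = 3.8%.

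| q | without a value | with a value | per predictor (20) |
|---|---|---|---|
| 5% | 10 | 198 | 9.9 |
| 10% | 21 | 187 | 9.4 |
| 20% | 42 | 166 | 8.3 |
| 30% | 62 | 146 | 7.3 |
| 40% | 83 | 125 | 6.2 |

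**3. 3A/3C if the time is imputed.** Counts are kept, but each patient in the second column receives a drawn remission time although the S-STS record shows no remission. Nothing in the imputation sentence restricts the draw to values beyond follow-up.

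**4. 3B/3D.** The Aims and hypotheses section speaks of "a greater risk of recurrence of PASI after complete remission (Hypothesis 3D"). Recurrence requires a prior remission, so every patient at risk has a remission time. Never-remitters are outside the risk set, and no regressor is missing.

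**5. Where the split's cut-off falls.** Illustrative simulation, N = 315: exponential remission times, 34% dropout spread uniformly over days 20 to 182, follow-up 182 days. Here q is the probability of not remitting by day 182. The dropout pattern is an assumption.

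| q | no observed date | median, remitters only (days) | Kaplan-Meier median (days) | lost before the Kaplan-Meier median |
|---|---|---|---|---|
| 10% | 56 | 42 | 55 | 15 |
| 20% | 89 | 52 | 79 | 25 |
| 30% | 120 | 58 | 106 | 38 |
| 40% | 149 | 62 | 138 | 53 |

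With a Kaplan-Meier cut-off, only the last column cannot be classified. All other undated patients are known to lie above it. At q = 50% the median is reached in only about half of the simulated trials.

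**6. What deletion from the split would cost.** Remission time exponential with mean 80·exp(0.5x) days, x a standardised baseline factor (time ratio exp(0.5) = 1.65 per SD), follow-up 183 days, no dropout; about 87% remit. Slower-minus-faster difference in x:

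- all patients, median of all (day 54): 0.64 SD
- remitters only, their own median (day 43): 0.44 SD, a loss of (0.64 − 0.44)/0.64 = 31%
- remitters-only median, non-remitters kept as slower: 0.61 SD, a loss of (0.64 − 0.61)/0.64 = 5%

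The loss comes almost entirely from deleting non-remitters. The shift of the cut-off contributes little.

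**The case against.** The strongest reply is that this is a condensed article. Censoring conventions and group assignment are usual content of an analysis plan that is not shown, the split is labelled secondary, and the study calls its p-values hypothesis-generating. That stands for much of the split. It does not dispose of 3A/3C: there the article itself fixes a continuous time as regressor, a generic imputation rule and an expectation of continuous suicidality, and these do not fit together. A later plan would have to qualify the published text.

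A reader might infer more than the document supports:

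- **That all of 3A to 3D are affected.** They are not; 3B/3D concern patients who have remitted.
- **That the split must drop non-remitters or invent a date.** It need not. If more than half remit, a patient followed for 6 months without an S-STS zero is simply above the median. The article nowhere says such patients are removed.
- **That the intent-to-treat sentence is contradicted.** That sentence names non-adherence and drop-out from clinical care. It does not address non-remission or missed research visits.
- **That the 34% attrition adds directly to the undated patients.** The article places the 30–35% dropout between discharge and month 6, so these patients can have a discharge S-STS and some may have remitted by then.
- **That predictors of slow remission are underestimated by a third.** That figure presupposes a deletion the protocol does not state.

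**Conclusion.** The point holds for the 3A/3C count models. A right-censored quantity is used there as a fully observed regressor, and neither complete-case analysis nor the stated imputation handles patients seen not to remit. Under an assumed 10% to 40% non-remission among completers, 21 to 83 of 208 are affected. Even 5% would take a complete-case fit below the plan's minimum of 200. These figures depend on q, which the article does not give.

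For the secondary split the point is one of clarification: the cut-off and the place of non-remitters need stating, and the reversed description of slow resolution needs reconciling. The fall from 0.64 to 0.44 SD applies only if non-remitters are deleted; with them kept as slower it is 0.61 SD. For 3B/3D there is no missing-regressor fault. The change should be made, but it does not threaten the study as a whole.

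**What to change.** 1. **3A/3C:** replace continuous time to remission with remission status at a fixed landmark visit, which non-remitters also have, or use another form that respects the censoring.
2. **Imputation:** state that observed non-remission is not missing data and that no remission time is imputed for such patients.
3. **Secondary split:** treat time to first S-STS zero as right-censored at the last S-STS visit and take the cut-off from the Kaplan-Meier median over all PP3 patients. Class as slower anyone still suicidal at a visit beyond it, whether or not they later remit or withdraw. Impute group membership only for those lost before the cut-off without remission. Say what will be done if the median is not reached.
4. **Direction:** reconcile the exploratory paragraph's description of slower resolution with the split, so that slower means a time above the median.

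The cost is analysis wording only, with no new data. The downsides are a group of early dropouts whose membership must be imputed (about 15 to 53 of 315 in the illustration) and some loss of information from using a landmark status instead of a continuous time.
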